## Abstract

**Methods:**

a prospective pragmatic trial will be carried out to describe the impact of an intervention on people aged>80, adjusted for relevant parameters: demographic variables, comorbidities, disability and bio-psycho-social frailty. They have been assessed with the Functional Geriatric Evaluation questionnaire that is a validated tool. Mortality, Acute Hospital Admission rates, Emergency Room Visit rates and Institutionalization rates are the main outcomes to be evaluated annually, over three years. Two groups of patients, made up by 578 cases (undergoing the intervention under study) and 607 controls have been enrolled and interviewed.

**Results:**

at baseline the two groups are quite similar for age, living arrangement, comorbidity, disability and cognitive status. They differ in education, economic resources and physical status (that are better in the control group) and in social resources (that is better in the case group). The latter was expected since the intervention is focused on increasing social capital at individual and community level and aimed at improving survival among the cases as well as reducing the recourse to hospital and residential Long Term Care.

**Conclusion:**

The proposed study addresses a crucial issue: assessing the impact of a *bottom up care* service consisting of social and health interventions aimed at reducing social isolation and improving access to health care services.

## I. INTRODUCTION

The implementation of effective community care services for older adults with disability or at risk of disability is a crucial point for improving older citizens quality of life and providing appropriate care at affordable costs [1]. In order to reach this objective, the stratification of older population according to risk of negative events (i.e functional status worsening, admission to hospital or to Long Term Care (LTC) residential facilities, death) and to amount of care demand is needed [2,3].

The most effective synthetic indicator of these two factors is bio-psycho-social frailty, that can be assessed with several validated instruments [4,5]. In fact, bio-psychosocial frailty is a multidimensional reversible condition predisposing to functional decline in older adults [6,7]. The assessment of frailty is associated to the risk of negative events as well as to the amount of the demand for care and it can address towards the most effective intervention. In fact, the frailty status is associated to a more urgent care demand, addressed mainly to LTC services, while the prefrail status could be effectively managed by prevention practices and active monitoring [8,9].

“Long Live the Elderly!” (LLE) is a Community-based pro-Active Monitoring Program (CAMP) born in 2003 to fight social isolation that is a risk factor for adverse events among older adults [10]. Social isolation represents an aspect of older adults frailty and it is related to the extension and quality of the individual’s relationship network. It is associated to higher risk of death, hospitalization and institutionalization [11]. During the 2003 summer a heat wave hit Southern Europe provoking about 20,000 of unexpected deaths, mainly among citizens over-74 living alone [12]. The LLE program is directed to over-74 years old citizens with a special focus on the over-80s because frailty is three folds higher among the over-74 compared with the 65 – 74 age group.

The general aim of the LLE program is to increase the social capital of both the community and the individual. The program provides phone monitoring to all the clients and home visits according to the individual’s needs. Moreover, it activates other formal or informal care resources according to the patients need reported in the Individualized Care Plan (ICP) which stems from the assessment of multidimensional frailty. The operators of the program are holders of at least a secondary school diploma and trained ad hoc for performing CAMP intervention. The main peculiarity of the program is that the operators identify the main problem of the client and try to track down the better solution in agreement with the client itself. It can be a health or social or a different kind intervention. Interventions may include the assistance to make safe the clients’ house thereby reducing risk factors for falls or revising the therapeutic scheme to improve the patient’s adherence to the treatment in collaboration with the GP. It is a *bottom up approach* [13] to overcome the separation between health and social care, that is still a burning issue at community care level in Italy as in many European countries. Some evidence seems to confirm the positive impact of the program on mortality, hospitalization and institutionalization [14,15]. The LLE program is operating in several Italian cities keeping on charge about 14,000 over-75 citizens. Aim of this paper is to describe the protocol of a study assessing the impact of a Community-based pro-Active Monitoring Program, on the quality of life and survival of people aged>80. The paper also provides information on baseline characteristics of the sample enrolled in the study.

## II. METHODOLOGY

The study is designed as a pragmatic trial comparing two groups of over-80s: the first one has been randomized among the LLE clients in two cities: Rome and Naples: the randomization has been performed on the LLE central database that includes all the participants to the program in Naples and Rome who have been administered the Functional Geriatric Evaluation (FGE) questionnaire [16,17], (3358 and 904 aged>80 people for Rome and Naples respectively). The entry point of the study is the administration of the FGE questionnaire. Periodical follow-ups are included in the program. The control group is selected by randomization from a pool of over-80s followed up by General Practitioners in the same cities who have been available to be involved in the study. Each GP provided a list of patients which 10 names have been selected from by randomization. The total pool consisted of approximately 8500 individuals. The sample was made up by 690 selected patients of which 83 (12.02%) refused to participate to the study.

The study has been approved by the Indipendent Ethical Committee of the University of Rome “Tor Vergata “ (R.S. 60/17). Participants gave their written consensus to participate to the study

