### Inclusion and exclusion criteria

People enrolled into the study must be older than 80 years old and had to answer to the FGE questionnaire. People living in an institution (nursing homes or similar) have been excluded. Advanced mental impairment was not an exclusion criteria, but in such cases the consent have been signed by the closest relative who also answered to the questionnaire on behalf of the participant; this modality is foreseen by the extensors of the questionnaire, just for these cases. The selected patients have been contacted by phone and they underwent a face-to-face interview by trained personnel in the GP’s outpatient facility or at home if they were unable to go out.

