The two groups show some differences as it occurs in a real world setting: in fact the two samples stems from the Community-based pro-Active Monitoring Program “Long Live the Elderly!” that is an ordinary service ongoing since 2004,, compared with an a cohort set up for this comparison. The main differences are about the physical condition area score, that is worse in the LLE group which at the same time shows higher social resources: this could be understandable since the LLE program is aimed at increasing the social capital at both individual and community level. We are probably witnessing one of the impacts of the program. It is also likely that individuals with advanced physical impairment can stay at home in case of the presence of a supportive social environment able to provide a certain amount of simple daily care. This is even more interesting because the LLE group shows a lower education level which is a proxy of the individual social and economic background with no great differences in the living arrangements. Cognitive and Functional area score have no significant differences between the two groups. It appears that the condition strictly associated to social background of the individuals are worse in the LLE group, so that the better score in the Social Area is due to other factors related to social relationships or to the intervention of formal care services catalyzed by the program.

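### The LLE group is drawn from existing clients with no stated limit on time since joining, so the pooled three-year contrast mainly describes continued membership and should not be reported without qualification as the programme's impact

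*Protocol article*

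**What the plan says.** All references are to the protocol article.

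- **Aim (Introduction).** To assess the impact of the programme on quality of life and survival in people over 80.
- **Source of the LLE group (Methodology).** "the first one has been randomized among the LLE clients in two cities: Rome and Naples". The frame is "the LLE central database that includes all the participants to the program in Naples and Rome who have been administered the Functional Geriatric Evaluation (FGE)". Its size is given as "3358 and 904 aged>80 people for Rome and Naples respectively".
- **Study entry (Methodology).** "The entry point of the study is the administration of the FGE questionnaire". The article does not link this date to the date of joining.
- **Eligibility (Inclusion and exclusion criteria).** "People living in an institution (nursing homes or similar) have been excluded". No criterion concerns time in the programme.
- **Outcomes (Abstract).** "Mortality, Acute Hospital Admission rates, Emergency Room Visit rates and Institutionalization rates are the main outcomes to be evaluated annually, over three years".
- **The programme (Discussion).** A service "that is an ordinary service ongoing since 2004", set against a control cohort assembled for this study. The authors think the LLE group's better Social Area score is probably already a programme effect. They add: "It is also likely that individuals with advanced physical impairment can stay at home in case of the presence of a supportive social environment".

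**The concern.** The effect of a programme is most directly estimated from people who start it, followed from the start. Here the intervention group consists of people who joined at some earlier, unreported time. A client who died, entered residential care or left before sampling is not in it, and any benefit or failure before study entry goes uncounted.

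Two mechanisms follow, with opposite signs. If the programme keeps frail people alive and at home, established clients will include frail people who would otherwise have been lost, and the contrast with controls shrinks. If clients in decline tend to leave, those remaining are healthier and the contrast is inflated. The pooled result cannot tell these apart.

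What is at stake is interpretation. A difference, or the lack of one, would be read as the effect of offering the programme to someone not yet in it, which is the question a health authority would ask.

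**Working it through.** **1. Was the LLE group exposed before baseline?** Three statements bear on this. The frame is all clients with an FGE, without a date limit (Methodology). The service dates from 2004 (Discussion). The authors attribute the baseline Social Area difference, 27.4 vs 22.0 in Table 3, to the programme (Discussion). A programme effect can be visible at baseline only if exposure came first, so on the authors' own reading at least part of the group had been exposed. How many, and for how long, is not reported. The frame holds 3358 + 904 = 4262 clients, of whom 578 (578/4262 = 13.6%) were enrolled.

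**2. Does the named adjustment resolve it?** The Abstract lists demographic variables, comorbidities, disability and bio-psycho-social frailty, but not time in programme. The FGE score includes socio-economic resources (Baseline assessment). If the programme has already moved the social domain, adjusting for the score may remove part of the effect.

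**3. The planning figure.** For death at 25% vs 18%, two-sided 5%, 80% power and pooled variance:

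n = [1.96·√(2 × 0.215 × 0.785) + 0.8416·√(0.25 × 0.75 + 0.18 × 0.82)]² / 0.07² = (1.1387 + 0.4872)² / 0.0049 = 539.5, so 540 per arm.

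This matches the Sample size section. With the enrolled 578 and 607, power is 83.5%. The arithmetic is sound. The question is which contrast the 25% and 18% refer to.

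**4. Direction of bias.** Both cases are illustrations on assumed inputs.

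*Inflation.* Suppose the programme has no effect, three-year mortality is 25% overall, a fraction f of clients left before sampling with risk r, and controls undergo no matching selection. Clients still enrolled then show (0.25 − f·r)/(1 − f):

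| f | r | Remaining clients | Controls |
|---|---|---|---|
| 0.10 | 0.35 | 0.215/0.90 = 23.9% | 25% |
| 0.20 | 0.45 | 0.160/0.80 = 20.0% | 25% |
| 0.30 | 0.45 | 0.115/0.70 = 16.4% | 25% |

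The last row is a spurious difference larger than the planned 25% vs 18%.

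*Shrinkage.* Let individual risk vary (gamma frailty, variance 0.5), with S(H) = (1 + 0.5H)⁻² and a conditional hazard ratio of 0.674. Ten years of prior membership and a control hazard of 0.213 per year give 25.0% over the next three years in surviving controls and 21.0% in surviving clients. The gap is 4 points instead of 7.

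**5. Can a size be stated?** No. In the shrinkage model, mortality over the first three of those ten years would be 1 − (1 + 0.5 × 0.639)⁻² = 42.6% without the programme and 1 − (1 + 0.5 × 0.674 × 0.639)⁻² = 32.3% with it. Mortality of 43% in controls some ten years younger, falling to 25% at study age, is not credible for this population. The model shows a direction only. The inflation table likewise depends wholly on f and r, which the article does not give.

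**6. What could recent entrants deliver?** For 25% vs 18% against 607 controls (two-sided 5%, normal approximation), power is about 31% with 100 recent entrants and 53% with 200. The 95% half-width for the difference is 1.96·√(0.18 × 0.82/m + 0.25 × 0.75/607): 8.3 points for m = 100, 6.3 for m = 200 and 4.7 for all 578.

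**The case against.** The authors are open about comparing an ordinary service with a purpose-built cohort, and a pragmatic study may do so. Several further objections carry weight.

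- **Unlimited membership length is inferred.** The article says nothing either way. The care plan stems from the frailty assessment (Introduction), so if the FGE used were always the one at joining, entry would be close to the start of individual care. The authors' remark on the Social Area score speaks against that, but the point is settled only by joining dates. Very long membership is also an edge case: the programme serves over-74s and mean LLE age is 84.8.
- **Controls are also survivors living at home.** Only selection that differs between the groups biases the contrast.
- **Residential care as both exclusion and outcome.** A reader might see a flaw here. There is none: someone already in an institution is not at risk of a first admission.
- **The Discussion's remark on staying at home.** A reader might infer that comparable unsupported people are in institutions and so missing from the controls. The authors do not say that. Their statement is hedged and concerns supportive surroundings in general.
- **A loss of power.** A reader might infer one from the planning rates. The Sample size section gives 18% for the population undergoing the programme, not for new clients, so no power loss follows.
- **Details may be elsewhere.** An analysis by time in programme could sit in a fuller document.

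What remains is that this article itself fixes both the sampling frame and the aim, and the pooled contrast from that frame is not the effect of starting the programme.

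**Conclusion.** The point holds as a limit on interpretation. On the frame as described, the pooled three-year comparison mainly describes continued membership among clients who have survived, remained in the programme and live at home. It should not be presented without qualification as programme impact. This rests on reading the frame as unrestricted in joining date, on former clients not being sampled, and on the authors' own view that a programme effect is visible at baseline.

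Neither the sign nor the size of the bias can be established from the article. The calculations above show that both signs are possible and should not be quoted as estimates. A reader might go further and conclude that the study can say nothing about the programme's impact. The article does not support that: recent entrants, if there are enough of them, bear on the effect of starting, and the pooled contrast is informative about staying, in each case subject to the groups being comparable.

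**What to change.** 1. Take each LLE participant's joining date from the LLE central database (assumed to be recorded there) and report the distribution of time in programme at study entry.
2. Keep the pooled comparison as the main analysis, but label it as the effect of continuing membership among people living at home, and qualify the stated aim and conclusions to match.
3. Pre-specify an analysis of the main outcomes by time in programme at study entry, for example up to 12 months versus longer. Present recent entrants against controls as a supporting estimate of the effect of starting.

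The cost is one variable, one stratified analysis and a change of wording, with no new recruitment. The drawbacks are that the number of recent entrants is unknown, their estimate will be imprecise, and stratifying does not remove differences in who chooses to join. For these reasons the recent-entrant contrast should support the main analysis and not replace it.

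### Study entry is set at the FGE, which LLE clients had before they were sampled and controls had afterwards; any gap up to consent is LLE follow-up in which death cannot occur

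*Protocol article*

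**What the plan says.** The Methodology section defines entry once, for both groups: "The entry point of the study is the administration of the FGE questionnaire".

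For the LLE group, the same section says that "the randomization has been performed on the LLE central database that includes all the participants to the program in Naples and Rome", and it limits that database to clients "who have been administered the Functional Geriatric Evaluation (FGE) questionnaire" (3358 in Rome, 904 in Naples). The Discussion describes the programme as a service "that is an ordinary service ongoing since 2004" and contrasts it with a control cohort assembled for this study.

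For controls the order is reversed. "Each GP provided a list of patients which 10 names have been selected from by randomization", and under Inclusion and exclusion criteria: "The selected patients have been contacted by phone and they underwent a face-to-face interview by trained personnel in the GP’s outpatient facility", or at home for those who could not go out.

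All participants gave written consent, through the closest relative in advanced mental impairment. Follow-up is six-monthly for three years, partly by telephone. The Sample size section makes mortality one of two components of the primary outcome. It expects 25% three-year mortality under standard care and at most 18% under LLE.

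**The concern.** When the clock starts before a person is selected, and selection requires that person to be alive, the time in between is immortal: it adds to follow-up but cannot contain a death. Under the stated rule, a control's clock starts after selection, at the interview. An LLE client's clock can start at an earlier programme FGE. Any such gap lowers LLE mortality in the analysis even if the programme has no effect. Adjustment for baseline covariates, which the Abstract plans, does not remove it.

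Mortality is the outcome mainly affected. An admission during the gap can still be counted from the regional database if the client survived to be sampled. Admission to long-term care would be affected in the same way as death if the exclusion of people living in institutions was applied at sampling.

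**Working it through.** **Order of events under the stated entry rule**

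| | LLE | Controls |
|---|---|---|
| First | FGE (condition for being in the sampling frame) | Random draw from GP lists |
| Then | Random draw from the database | Telephone contact, then face-to-face interview |
| Date of consent relative to the above | Not stated | Not stated; refusal follows selection |
| Clock starts | FGE, before the draw unless repeated | Interview, after the draw |

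The account of selected patients being telephoned and interviewed fits controls best. The interview site is the GP's facility, and the only selection and refusal counts given are for controls: 690 − 83 = 607.

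**The plan's own figure**

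Inputs from the Sample size section: p1 = 0.25, p2 = 0.18, alpha 5% (taken as two-sided), power 80%. With the pooled-variance formula and mean p = 0.215:

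n = [1.960 × √(2 × 0.215 × 0.785) + 0.842 × √(0.25 × 0.75 + 0.18 × 0.82)]² / 0.07² = 540 per arm.

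This matches the stated 540. Hospitalization (35% against 25%) needs only 329 per arm, so death determines the sample size.

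**Effect of a gap when the programme does nothing**

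Assumptions: a constant hazard, the same gap of g years for every LLE client, and survival through the gap required for inclusion. The gap is not in the document, so g is varied.

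- Hazard: h = −ln(0.75)/3 = 0.0959 per year.
- Apparent three-year LLE mortality counted from the FGE: 1 − exp(−h(3 − g)) = 1 − 0.75^((3 − g)/3).
- Apparent death-rate ratio: deaths divided by person-years including the gap, relative to h. Person-years per client are g + [1 − exp(−h(3 − g))]/h.
- Chance of a significant mortality result favouring LLE: two-proportion test with 578 LLE clients and 607 controls, controls at 25%.

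| Assumed gap | Apparent LLE mortality | Rate ratio (true value 1) | Chance of false significance favouring LLE |
|---|---|---|---|
| 0 | 25.0% | 1.00 | 2.5% (half of the two-sided 5%) |
| 3 months | 23.2% | 0.91 | about 11% |
| 6 months | 21.3% | 0.82 | about 32% |
| 12 months | 17.5% | 0.65 | about 89% |

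The gap that gives exactly the planned 18% is g = 3 + ln(0.82)/0.0959 = 0.93 years, about 11 months.

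**The case against.** The strongest reply is that the article does not date the LLE FGE or the LLE consent, so no gap is demonstrated. Entry point may mean only the qualifying step, since answering the FGE is an inclusion criterion. Follow-up is described separately and in the future tense, and the Abstract calls the study prospective and says that both groups were enrolled and interviewed. For impaired participants, the relative who signed consent also answered the questionnaire, which suggests that consent and FGE could be one occasion. The Discussion reads the better LLE social score as a probable programme effect, which implies that the FGE used was taken after exposure had begun. The database is not said to be limited to living clients. Finally, a condensed article may leave exact time-origin rules to the full protocol.

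Much of this stands. A reader might infer that LLE mortality is in fact lowered, or that a gap of about a year accounts for the planned effect. The document supports neither: 3, 6 and 12 months are assumed values, and a service running since 2004 says nothing about how old the sampled FGEs are. Nor does the document establish that clients who had died could not be drawn.

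It does not dispose of the point. The article itself states the entry rule and itself makes a prior FGE the condition for LLE sampling. No passage says that the FGE was repeated at enrolment, that LLE consent was taken at the FGE, or that the LLE clock starts later. A draw that included clients already dead fits poorly with telephone follow-up. A post-exposure FGE is not the same as one taken at the draw.

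**Conclusion.** The concern holds in conditional form. As written, the entry rule lets LLE follow-up begin before selection while control follow-up begins after it. Unless the FGE was repeated in LLE clients at enrolment, or consent was taken at the FGE and clients who had since died could still be drawn, mortality is biased in favour of LLE. The direction follows from the text; the size does not, because it depends on an interval that is not reported. Under the assumptions above, the bias runs from nothing with no gap, through 1.8 percentage points at 3 months and 3.7 at 6 months, to about 7.5 at 12 months. The planned difference is 25 − 18 = 7 points. The rule should be corrected before mortality is analysed, because it bears on the outcome that determines the sample size.

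**What to change.** - Set time zero in both groups at written consent (or at the random draw), and count the three years and all events from that date. Alternatively, keep the FGE date as origin and let LLE clients enter the risk set only at consent (delayed entry).
- Report the FGE-to-consent interval by group.
- Add a sensitivity analysis restricted to LLE clients whose FGE was close to consent. Moving time zero alone would leave some LLE covariates measured well before it, while control covariates are measured about when they are enrolled, and the planned adjustment relies on these variables.
- State that the LLE group consists of current (prevalent) clients and limit the conclusion to them. Neither choice of time zero restores clients who died or left before sampling.

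The cost is protocol and analysis-plan wording, one date variable per participant and one extra analysis. No new participants are needed. If the gap proves to be zero, the primary result is unchanged; if it is not, the LLE mortality result may look less favourable.
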